**Methods:**

A multi-center exploratory randomized controlled trial, with a 4-week follow-up period, will be conducted in three major public psychiatric hospitals in Guangdong, China. Participants in the control group will be assigned to routine dysphagia care, while participants in the intervention group will undergo the same nursing care and additionally receive the SST program. The SST program includes five sections of swallowing organs training: lip movement, facial movement, tongue movement, mandibular movement, and neck movement. Primary outcomes evaluate the swallowing function, namely, Water Swallowing Test (WTS) and Standard Swallowing Assessment (SSA). Secondary outcomes aim at measuring the improvement of negative impacts of dysphagia, namely eating behavior, ability of daily activity, and nutritional status. Data will be collected at baseline (*T*_1_), at 2 weeks (*T*_2_, intervention), and 4 weeks after intervention (*T*_3_, follow-up).

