**Discussion:**

This study will offer trial-based evidence of the effectiveness of SST in relieving dysphagia among AD patients. SST program is expected to improve both the swallowing function and reduce the negative impacts of dysphagia, with an exploration of acceptability in the SST program.

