### Outcomes

Study outcomes will be evaluated by trained research assistants who are not aware of group allocation. The time points for measurement will be at baseline (*T*_1_, day 0), 2 weeks after intervention (*T*_2_, day 14), and 4 weeks after intervention (*T*_3_, day 28). The schedule of outcome measurement is presented in Fig. 3.

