#### Primary outcomes

Water Swallowing Test (WST), a five-level water drinking test, will be used to determine the effectiveness of SST. Evaluators observed individual reactions after drinking 30 ml of water (complete recovery: swallowing without cough; improved swallowing function: occasional choking, and invalid: unchanged or worse swallowing function). Effective rate = (completed recovery + improved swallowing function)/total cases in each group *100%. The sensitivity and specificity of WST ranged from 34.8 to 55.7% and 78.9 to 93.2% in older adults [20].

On basis of WST, Standard Swallowing Assessment (SSA) will be performed to evaluate the severity of dysphagia. The score of SSA ranged from 18 to 46, and a high SSA score reflected serious dysphagia. SSA exhibited a specificity of 0.90 and a sensitivity of 0.97 in detecting dysphagia, with positive and negative predictive values of 0.92 and 0.96 [21].

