### Sample size

The sample size was calculated based on the comparison of WST. By using G*Power 3.1 software, we set a significant difference of 14.2% (74.2% in the experimental group and 60.0% in the control group), an alpha error of 0.05, a beta error of 0.80, and the effect size *f* = 0.32. After calculation, a total sample size of 78 was required. To accommodate for a 20% attrition rate and other confounding factors, we recruited 100 participants. After obtaining informed consent, each involved hospital was allocated to the intervention group or to the control group in a 1:1 ratio.

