### Statistical methods

Exploratory data analysis and Shapiro-Wilk tests will be performed to determine the normality of data distribution. Continuous variables will be expressed as means with standard deviations or medians with interquartile ranges; mean differences will be expressed from baseline to the end of the study. For categorical variables, counts and percentages will be presented, and between-group comparisons at baseline will be tested with the *x*^*2*^ test [25]. Between-group differences at baseline, and in the change from baseline to the end, will be tested with repeated measure analysis of variance. An analysis of covariance will be used to adjust for baseline cognitive functioning. Paired *t*-tests will be performed for between-group comparisons from the baseline to the end. The level of significance will be set as a two-sided *P* value less than 0.05. Data analysis will be conducted using SPSS version 20.0 with intent-to-treat analysis (ITT) and per-protocol (PP) analysis. The results of the ITT analysis will be compared with those of the PP analysis to determine the consistency.

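### Two primary outcomes share one undivided 0.05 level with no success rule; if either may carry the effectiveness claim, the two-sided error is about 7–10%, not 5%

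*Protocol article*

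**What the plan says.** All references are to the protocol article.

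- **Two primaries.** Abstract, Methods: "Primary outcomes evaluate the swallowing function, namely, Water Swallowing Test (WTS) and Standard Swallowing Assessment (SSA"). The Primary outcomes section describes both and ranks neither. WST is summarised as a responder proportion, "Effective rate = (completed recovery + improved swallowing function)/total cases in each group *100"%, with no visit named.
- **One threshold.** Statistical methods: "The level of significance will be set as a two-sided *P* value less than 0.05". No adjustment, order or success rule is given.
- **The contrast.** Statistical methods: "Between-group differences at baseline, and in the change from baseline to the end, will be tested with repeated measure analysis of variance", and "mean differences will be expressed from baseline to the end of the study".
- **Visits.** Outcomes: "2 weeks after intervention (*T*_2_, day 14), and 4 weeks after intervention (*T*_3_, day 28").
- **Sizing.** Sample size: "The sample size was calculated based on the comparison of WST".
- **The claim.** Abstract, Discussion: "This study will offer trial-based evidence of the effectiveness of SST in relieving dysphagia among AD patients". The Objectives section likewise sets out to evaluate effectiveness. The Trial design section calls the trial exploratory.

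**The concern.** With two primary outcomes of equal standing and an unsplit level, the 5% describes each test and not the conclusion drawn from the pair. Nothing in the article prevents effectiveness from being concluded from WST alone, from SSA alone, or from whichever is significant. Sizing on WST does not settle this, because SSA keeps its primary label.

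At stake is how a split result would be read. If one primary is significant and the other is not, the article does not say whether the trial has succeeded, and the choice would be made with the data in view.

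**Working it through.** **Inputs**
- Primary outcomes: 2 (Abstract, Methods; Primary outcomes).
- Level: two-sided 0.05 per test (Statistical methods).
- Contrast: change from baseline to the end of the study, so one test per outcome (Statistical methods).
- Correlation between the two test statistics under no effect: not given. Assumed 0 to 0.9.
- Effect size f = 0.32, required total N = 78, power taken as 0.80 (Sample size, where 0.80 is labelled a beta error).

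**Step 1. The plan's own figure.** The article states no overall error rate. The figure that can be reproduced is N = 78. The noncentrality is 78 × 0.32² = 7.99. At two-sided 0.05, a two-group F test then has 79.7% power and a 1-df chi-square test 80.7%. So N = 78 corresponds to one comparison at the full 0.05.

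**Step 2. Either outcome suffices, two-sided.** If independent, the error is 1 − 0.95² = 0.0975. If correlated, it is 1 − P(|Z₁| < 1.96 and |Z₂| < 1.96) for bivariate normal Z.

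| Correlation | Two-sided error, either outcome |
|---|---|
| 0 | 9.75% |
| 0.5 | 9.1% |
| 0.7 | 8.3% |
| 0.8 | 7.8% |
| 0.9 | 7.0% |

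**Step 3. Direction of benefit only.** A false claim of benefit needs a significant result in favour of training, which has probability 0.025 per outcome. If independent, the chance on either is 1 − 0.975² = 0.0494. At correlation 0.9, 1 − P(Z₁ < 1.96 and Z₂ < 1.96) = 0.035. The benchmark here is 2.5%, so the relative inflation is about 1.4 to 2 times, as in Step 2.

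**Step 4. Both outcomes must succeed.** The chance that both are falsely significant cannot exceed that of either one, so it is at most 5%.

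**Step 5. Cost of a correction.** With Holm, the smaller P value is compared with 0.05/2 = 0.025. At noncentrality 7.99, power for one outcome at 0.025 is 70.5% (F) or 72.1% (chi-square), against 79.7% and 80.7% at 0.05.

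**The case against.** **The trial is labelled exploratory, the article is condensed, and the SAP is not shown.** Success rules are often left to a SAP, and an exploratory trial does not need confirmatory error control. This has weight and is why the point is not a critical one. It does not dispose of it: the article itself fixes two equal primaries and one undivided level, and it promises evidence of effectiveness.

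**The either-outcome rule is an assumption.** That is correct. The article states a significance level and no success rule, so the 7–10% is conditional on that reading.

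**Two-sided error overstates the risk of a false claim of benefit.** Also correct. The directional figures in Step 3 answer it, and the relative inflation remains.

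**Stronger readings the text does not support.**
- A reader might count four tests, two outcomes at two visits, which gives 18.5% if independent. Measuring at T2 is not testing at T2. The Statistical methods section sets the contrast as baseline to end and plans no separate 0.05 test at T2. Four independent tests would also be implausible for two swallowing measures taken on the same patients two weeks apart.
- A reader might treat the per-protocol analysis as a second route to a positive result. The article gives its purpose as a check of consistency with the intention-to-treat result.

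Some doubt about the time point does remain. The WST effective rate names no visit, and T3 is described both as four weeks after intervention and as day 28, although the Interventions section gives four weeks of training.

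**Conclusion.** The point stands and should be addressed. The overall error for a claim resting on either primary is about 7–10% two-sided for the baseline-to-end contrast, or about 3.5–4.9% in the direction of benefit against a nominal 2.5%. This rests on two assumptions: a significant result on either outcome counts as success, and the correlation between the two tests lies between 0.9 and 0. If both outcomes must be positive, the error is at most 5%, but the article does not say that they must. The fault is an unstated success rule combined with an unsplit level. It is not a plan for repeated testing across visits or analysis sets.

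**What to change.** State that effectiveness is judged on the end-of-study (T3) contrast in the intention-to-treat set, in one of two ways:

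1. WST, the outcome used for sizing, is the single primary at two-sided 0.05, and SSA becomes secondary.
2. Both remain primary under Holm: the smaller P value is compared with 0.025 and, only if that is significant, the other with 0.05.

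In either case, say that T2, per-protocol and secondary results are supportive, reported with 95% confidence intervals and without an effectiveness claim. The descriptions of T3 as four weeks after intervention and as day 28, alongside four weeks of training, must be reconciled so that the end-of-study time point is unambiguous.

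**Cost.** A few sentences of text. Option 1 costs no power on WST but gives up SSA as a basis for the claim. Option 2 lowers first-step power from about 80% to about 70–72% at f = 0.32 and N = 78. Those power figures take f = 0.32 at face value. The same section's rates, 74.2% and 60.0%, give only about 26% power with 39 per arm at 0.05. That conflict is a separate matter, to be settled before the power cost is quoted.

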### Study quality control

The validity and reliability of the instruments used in this study have been examined. The psychiatric hospitals involved in this study are qualified in research and geriatric mental care and can offer adequate support. To improve homogeneity, all research assistants will receive unified training for proper assessments and check the questionnaire; the intervention will use standardized teaching videos and instruction. Moreover, the primary researcher will check the videos recorded during the intervention twice weekly for the performance adherence of patients and the staff.

## Discussion

This protocol presents a multi-center and exploratory RCT to assess the effectiveness of progressive swallowing exercises on swallowing function, daily activity life, and eating behaviors in AD patients in Guangdong, China. The intervention program addresses five main swallowing muscle groups and will be taught stepwise.

### Monitoring

Adverse events, data collection, maintenance of data confidentiality, and data analysis will be monitored by the Department of Research Project Administration of GZ. A research assistant will be assigned to each hospital to conduct a biweekly review of the study progress and any adverse events of this study. Any unexpected event will be directly reported to the Department of Research Project Administration of GZ.

### Risks, burdens, and benefits

The intervention will be implemented based on the patient’s physical condition. The physical and emotional distress induced by the intervention (e.g., an increase in respiratory and heart rates) are assumed to fall within the range of a normal reaction. To reduce the discomfort during SST, research assistants will maintain participants’ hydration and ensure appropriate rest. In a previous study, the Water Swallowing Test score and Barthel Index improved after intervention [26]. This study has been assessed by the ethical department in Guangzhou mental health center as a non-invasive program. Based on these assessments, the training program designed for dysphagia is not harmful to AD patients.

Before commencement, to avoid the risk of medical emergencies during the implementation, the nurses and research assistants will be instructed about the safety considerations and safety protocol. The caregivers or family members will respond to the questionnaire, while the participants will undergo the cognitive function test, that is, MMSE. Participation in the study will provide no direct benefit to the respondents.

### Modification and inquiry

Any modification or inquiry regarding the study will be discussed through the Affiliated Brain Hospital of Guangzhou Medical University. During the study period, inquiries from the patients and their families will be gathered and solved by research assistants.

### Confidentiality

The participants’ personal data, including names, addresses, and telephone numbers, contained in the consent form and case report form will be anonymized using a research ID number and stored on a secured computer database. Research data will be monitored by the Department of Research Project Administration of GZ and will only be accessed by authorized members of the trial team.

### Post-trial care

If the study demonstrates no negative effects, participants in the control groups will be invited to participate in SST program after the study timeframe.

### Dissemination policy

The results will be disseminated to professionals and hospitals in geriatric and mental care in Guangdong province. The findings will also be disseminated to peer-reviewed scientific journals and presented at academic conferences.

## Trial status

This manuscript describes the SST trial protocol version #1 dated February 6, 2022. Recruitment started in March 2022 and the anticipated completion is March 2023.

## Data Availability

The datasets will be available from the corresponding author on reasonable request.

## Abbreviations

GDP: Gross domestic product
SST: Stepwise Swallowing Training
RCT: Randomized controlled trials
MMSE: Mini-Mental State Examination
WST: Water Swallowing Test
SSA: Standardized Swallowing Assessment
AEBQ: Abnormal Eating Behavior Questionnaire
MNA-SF: Mini Nutritional Assessment - Short Form
VFSS: Video Fluoroscopic Swallowing Study
BI: Barthel Index
ITT: Intention-to-treat
PP: Per-protocol
